### Monitoring

2.5

This study did not incorporate external professionals for data monitoring. Instead, data monitoring is carried out by an internal Data Monitoring Committee, integrated by (1) the research coordinator of the study, (2) the research co-coordinator, and (3) the data-analysis professional. Participant monitoring is carried out weekly by telephone on a non-therapy day, which allows us to promote participant retention and encourage participants to complete the follow-up. The following information is recorded: (1) unusual or new neurologic symptoms, (2) adverse events such as falls, (3) level of pain experimented during the week, (4) medical appointments and motive, (5) changes in medication; (6) level of physical activity outside of the study, (7) mood, anxiety, and depressive symptoms during the week and, (8) individual perception of the evolution process. The Data Monitoring Committee will decide whether trial participation should be discontinued, based on monitoring reports. If participants decide to withdraw, the Data Monitoring Committee will be in charge of collecting the reasons for abandonment.

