### Assignment of intervention and blinding

2.3

A stratified randomization process will be performed by the external research, considering the H&Y stages. Because patient recruitment will occur over a prolonged period, to control the stratification, the randomization will be performed after 12 participants group recruitment, and this process will be repeated six times, with the exception that the last group of recruitment will be of 14 people instead of 12. The allocation in each group of recruitment will be 1:1, using a function of Microsoft Excel (V18.0, 2021. Excel; Microsoft Corp). To ensure masking, the raters physiotherapist, and data analysis researcher, will be blinded to the participant’s allocation. Although participants and treating physiotherapists cannot be totally blinded to the intervention performed, the hypothesis and objectives of the study will be hidden from them. At the same time, all participants will be instructed not to disclose information regarding their intervention to the raters’ physiotherapists. To control expectancy effects, it will be explained to patients that it is not yet determined which therapy is more effective. On the other hand, a consecutive number code will be assigned to the participants without disclosing the treatment group to which they belong.

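### The data analyst declared blinded in 2.3 appears, in 2.5, on the internal committee that decides individual discontinuation from participants' weekly reports, so analyst blinding is unprotected and removals could depend on perceived response or arm

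*Protocol article*

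**What the plan says.** On masking, section 2.3 (Assignment of intervention and blinding) states: "To ensure masking, the raters physiotherapist, and data analysis researcher, will be blinded to" the allocation. The same section concedes that "participants and treating physiotherapists cannot be totally blinded to the intervention performed". It then restricts what participants may say, but only towards one group: "all participants will be instructed not to disclose information regarding their intervention to the raters" (the assessing physiotherapists). Participants carry a number code that does not show their group.

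On monitoring, section 2.5 states: "This study did not incorporate external professionals for data monitoring". An internal committee does the work instead. Its members are listed as "1) the research coordinator of the study, (2) the research co-coordinator, and (3) the data-analysis professional".

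The committee's input is described as follows: "Participant monitoring is carried out weekly by telephone on a non-therapy day". Eight items are recorded, among them new symptoms, adverse events, pain, medication changes, outside activity and mood. The last is "8) individual perception of the evolution process". Its power over individuals is stated as "The Data Monitoring Committee will decide whether trial participation should be discontinued, based on monitoring reports". It also collects the reasons when participants withdraw.

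On analysis, section 2.4 applies intention-to-treat principles, but words this as conditional on adherence problems arising. Section 3 describes trial data in general as blinded and encrypted.

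**The concern.** Raters and analyst are the two roles that 2.3 blinds to allocation. The title of the blinded analyst in 2.3 and the title of the third committee member in 2.5 are nearly identical, and no second analyst is mentioned. If they are the same person, someone who must not know the arm takes part in case-by-case decisions that use what unblinded participants have said over the telephone.

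Two things are at stake. The first is analyst masking. Under 2.4 the analyst still has to judge model assumptions and choose unspecified corrections, which is where knowledge of the arm could matter. The second is selection. If the decision to end someone's participation can draw on perceived progress, and that person's gait speed at t1 is then not measured, the set of people with a primary outcome can depend on response. It can also depend on arm if the arm becomes known.

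**Working it through.** The plan gives no figure on this point, so the main check is to set the statements side by side.

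**1. Roles.** Section 2.3: the analyst is blinded. Section 2.5: a data-analysis professional is one of three committee members. That this is one person is the natural reading, but it is not stated.

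**2. Information reaching the committee.** Decisions rest on monitoring reports. The reports originate with participants who know their intervention: relaxation on a stretcher and imagery occur only in the GAITimagery group (2.2.2). Two of the eight recorded items, mood and perceived evolution, invite comment on the therapy.

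**3. Barriers between that information and the analyst.** The non-disclosure instruction names only the raters. The person making the calls is not identified. The number code and the general statement in section 3 conceal a group label; they do not conceal what a participant says. Nothing states that reports are masked before the committee sees them.

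**4. Occasions for removal.** Section 2.2.1 includes conditions that run on after randomisation: stable medication until t2, and no other physical therapies or sports during the trial. The calls record both medication changes and outside activity. Grounds for removal will therefore come before the committee, in the same record as perceived progress. The article does not say whether perceived progress plays any part.

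**5. What happens to the data of those removed.** Section 2.5 speaks of ending trial participation and does not say whether t1 and t2 are still measured. The mixed MANOVA in 2.4 uses t0, t1 and t2. A conventional fit needs complete records, so a person without t1 or t2 would drop out of it. Handling of missing data may be set out in a plan not shown, but no analysis recovers a t1 gait speed that was never measured.

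**6. Illustration of size.** Only the 44 per group comes from the document (2.2.4). The removals below are assumptions, all in one arm, with no true effect.

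- *Mild case.* Three of 44 leave, each 1 SD below the arm mean. Shift in the mean of those left = 3 × 1/(44 − 3) = 3/41 = 0.073 SD. The standard error of the difference is √(1/41 + 1/44) = 0.217 SD, so the shift is 0.073/0.217 = 0.34 standard errors. The two-sided 5% error becomes P(Z > 1.96 − 0.34) + P(Z < −1.96 − 0.34), about 6.3%.
- *Extreme case.* The worst r of 44 responders leave. Approximate bias = φ(c)/(1 − q), with q = r/44 and c = Φ⁻¹(q). The error rates come from 40,000 simulated two-sample t-tests.

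| Removed (r) | Bias (SD) | Two-sided error |
|---|---|---|
| 0 | 0 | 5% |
| 1 | 0.06 | 6% |
| 2 | 0.10 | 8% |
| 4 | 0.18 | 14% |
| 8 | 0.32 | 34% |

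These figures show what selective removal could do if those removed were left out of the analysis. They do not predict that it will happen.

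**The case against.** A reader might infer that analyst blinding is already lost because the analyst reads a narrative account from every participant each week. The documents do not support that. The article lists recorded items, some of them as levels, which fits a structured form. It does not say that the reports reveal the arm, that the committee is unblinded, or that each member reads each record. Assessments are coded, and data are described as blinded. An article may also leave the format of the calls to a fuller protocol. This stands, and it limits the point to missing protection.

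A reader might also infer that the committee removes people at will and that the analyst then works only on those who remain. That goes too far as well. Several recorded items correspond to conditions in 2.2.1, perceived evolution is one item of eight, and nothing says that it drives removal. Intention-to-treat is named, and the calls are meant to promote retention. If discontinued participants were still assessed and analysed as randomised, the selection bias illustrated here would not arise. What weakens this defence is that the intention-to-treat sentence is conditional and is not tied to committee decisions.

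Other safeguards deserve credit. The hypothesis is withheld from participants and therapists, patients are told that neither therapy is known to be better, and the primary outcome is measured by instrument. These reduce expectancy and rating bias. They do not bear on who is removed or on what the analyst learns.

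Finally, the mild illustration moves the error rate only from 5% to about 6.3%, and its inputs are assumed. That is correct, and the illustration should not be used to argue severity.

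**Conclusion.** The conflict of roles between 2.3 and 2.5 is real and should be resolved. Analyst blinding is unprotected, and discontinuation decisions could depend on perceived response or arm. The conclusion rests on reading the two near-identical titles as one person, which is likely but not stated. The selection part also assumes that some people the committee discontinues would lack t1 or t2 data or be left out of the analysis.

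No size can be derived from the documents. Under the assumed removals the bias runs from about 0.06 to 0.32 SD. Such shifts would matter in a trial planned on a small expected effect (f = 0.15 in 2.2.4), but the number and pattern of removals are unknown. Confidence is high on the role conflict and moderate on its effect. This is a change that should be made, not evidence that the trial is compromised.

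**What to change.** Reconcile 2.3 with 2.5 as follows.

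1. Keep the blinded analyst out of individual discontinuation decisions, or give that committee member only coded, arm-free summaries.
2. Extend the non-disclosure instruction in 2.3 from the raters to everyone who must stay blinded.
3. State in 2.5 that participants whom the committee discontinues are still assessed at t1 and t2 and analysed as randomised, unless they withdraw consent.
4. Have the sponsor set its discontinuation criteria in advance and say whether perceived progress plays any part. What those criteria should be is a clinical matter for the sponsor, and no stopping rule is proposed here.

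The cost is protocol wording and a change of committee role. The t1 and t2 assessments are visits already planned. The small downside is that the analyst can no longer help with individual decisions.

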### Patient and public involvement

2.6

Patient and/or public were not involved in the design of this protocol.

## Ethics and dissemination

3

All procedures were approved by the Ethics Committee of Research in Humans of the Ethics Commission in Experimental Research of University of Valencia on February 11, 2021 (Register number 1557673), in accordance with the principles of the World Medical Association’s Declaration of Helsinki, the Council of Europe Convention regarding human rights and the requirements established in Spanish legislation in the field of Biomedical research, personal data protection and bioethics. We did not consider future changes in the study protocol reported by the committee. Eligible participants are informed about the study and the privacy protection concept before participating. The physiotherapists in charge of assess the eligibility criteria will be responsible for obtaining the written informed consent (Supplementary material 3) from the participants before the first tests started. All the data and information collected regarding this trial are treated confidentially (blinded and encrypted) by the researchers connected to the study. Finally, all results from the trial will be published in international peer-reviewed scientific journals, regardless of whether these results are negative or inconclusive.

## Discussion

4

This study protocol aims to determine the improvements in gait rehabilitation in people with PD, who integrate MI techniques into the treatment compared with a group gait training without MI. Functional neuroimaging has documented that MI and motor execution activate similar cortical networks as the primary motor cortex and pre-motor areas, including the supplementary motor area (11, 13, 62). Based on this, the MI could be especially useful in people who need to correct or reinforce movement patterns due to motor disorders, facilitating the right execution. Previous randomized control trials have studied the effect of gait physiotherapy with and without MI in their protocols, with no statistical differences between groups (14–17). This lack of differences that support the clinical decision to integrate MI into routine practice, may arise because of different methodological approaches. The first of them is the quality of the vividness that the participants have during the imagery exercise, conditioned by the inclusion of the AO phase. Since the patients must imagine a corrected movement pattern, education on the gait cycle is essential to ensure the integration of the betterment of gait in the posterior physical performance. Therefore, not including AO in the MI protocols (16, 17) may cause the control groups to not differ from the experimental groups reported. Similarly, to ensure the sharpness of MI in our protocol, we include an intra-session monitoring measure to verify that participants are achieving sufficiently effective imagery. Also related to the effectiveness of the vividness, the severity of the disease, and the appearance of cognitive impairment, may influence the superiority of physical therapy with MI. From the studies reviewed, two samples studied have a Montreal Cognitive Assessment score < 26 (14, 15), which implies cognitive impairment (63). On the other hand, when the studies evaluated cognition through the MiniMental State Examination, the participants could also present a wide range of cognitive performance with a normal score, even including a level of impairment consistent with dementia (64), due to the poor sensitivity for detecting cognitive impairment (including mild cognitive impairment) in PD, by comparing it to the Montreal Cognitive Assessment (65–67).

Apart from cognitive status, the assessment instruments used, and their ability to detect small changes, are relevant when analyzing the possible superiority of physical therapy interventions with MI compared to programs without MI. In this regard, scales and questionnaires, evaluated by a professional or self-reported by the participants, have a subjectivity bias and could be less sensitive to change (68), besides the ceiling effect that these tools have, which is accentuated in the evaluation of patients who have minimal or mild gait disturbance. From the previous results reported, Santiago et al. (15) evaluate the kinematics gait with a Motion Capture System, reporting a hip range improvement of 6.5%. The GAITimagery protocol includes the assessment with dynamometric platforms and inertial sensors that allow us to register spatiotemporal, dynamometric, and kinematics parameters from the gait performance. Likewise, we also incorporate common clinical measurement questionnaires and scales that will enable us to analyze the different percentages of improvement measured with both tools systems, psychometric and instrumental. In line with the measured variables, the primary outcome to estimate the sample size used in previous protocols of MI and physiotherapy of gait for people with PD, were the Hip range of motion (14, 69), the Visual analog scale of walking (16), the Functional independence measurement scale, and the UPDRS (35). On the other way, the primary outcome of the GAITimagery trial is gait speed, considered the most powerful biomarker of mobility (70), and is an objective parameter that does not depend on the evaluator, as clinical scales do. In this sense, the GAITimagery protocol will provide an objective and portraying parameter during PD course (26) for sample size estimation for future researchers.

Despite not reporting differences between groups, previous studies informed that gait physiotherapy with MI causes statistical changes in the total score of MiniBEST test, the Sensory orientation and Dynamic gait domain of balance assessment (14), the hip ROM, time of stance and swing phase of gait cycle (15), the mental section from UPDRS, and Schwab and England scale score for Activities of daily life (17). Furthermore, other authors have been informed of improvements in the Timed Up and Go test, the 10-meter walking test, and the score in the MiniBest balance test (20) when combining MI with dual-task; and MI combined with Neurofeedback has demonstrated improvement in endurance walking (23).

Even when we hypothesize that MI added to gait training could achieve a greater effect than detached gait training in people with PD, several factors or possible covariates must take into account to control the influence on the variance in dependent outcomes, such as the number of training sessions completed, average time elapsed between the medication doses intake and the start of the physiotherapy sessions, the stage of PD severity, and other between-groups factors like sex or level of activities in daily life, as the GAITimagery protocol contemplate. The methodological considerations that the GAITimagery trial has incorporated in the future development of this trial will allow us to analyze the effects of MI techniques in physiotherapy. The MI is an easily transferable to clinical practice technique because it does not require expensive materials or additional training for therapists, unlike other strategies such as neurofeedback or virtual reality. Nevertheless, it is necessary to study the ratio of gait improvement that can be explained by the MI aside from its superiority compared to not including MI in physiotherapy programs.
